## Abstract

**Background:**

Most antibiotic prescriptions for acute cough due to lower respiratory tract infections (LRTI) in primary care are not warranted. Diagnostic uncertainty and patient expectations and worries are major drivers of unnecessary antibiotic prescribing. A C-reactive protein (CRP) point of care test may help GPs to better guide antibiotic treatment by ruling out pneumonia in cases of low test results. Alternatively, enhanced communication skills training to help clinicians address patients' expectations and worries could lead to a decrease in antibiotic prescribing, without compromising clinical recovery, while enhancing patient enablement. The aim of this paper is to describe the design and methods of a study to assess two interventions for improving LRTI management in general practice.

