#### Secondary outcome measures

1. Clinical recovery and return to usual activities

2. Cost-effectiveness of point of care CRP and communication training

3. Patient enablement, satisfaction and future consulting intention

4. Diagnostic testing other than point of care CRP

5. Use of health services, including re-consultation

6. Subsequent antibiotic prescribing rates within 28 days of the initial consultation

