### Data collection

Sequential elegible patients will be asked by their GP to participate. During this consultation, the GP will take written consent and note the inclusion criteria on the trial inclusion form. The practice nurse will give each participant a simple self-complete symptom diary after the consultation. After general questions on cough and the consultation, patients will be asked each day to complete a 6 item scale, with responses to statements ranging from 0 to 6. A total symptom score will be derived from this scale. Items relate to coughing, phlegm, shortness of breath, sleep disturbance, impairment of normal daily activities, and generally feeling unwell. This symptom diary has previously been used in a large LRTI study[35]. Patients will then be followed-up for 28 days, or if still unwell, until recovered with a maximum follow up of ten weeks. Furthermore, weekly questions will record time off work, medication use and re-consultation. The recruiting GP will fax the informed consent form and inclusion form to the research team in Maastricht on the day of inclusion. The clinical effectiveness analysis will be based on diary responses. A single Likert type scale response item will assess satisfaction with the consultation. Patient enablement will be measured using the Patient Enablement Instrument [36] translated into Dutch. Concurrent validation will be undertaken. In addition, the research team will retrieve data on diagnosis, antibiotic prescription, re-consultation, diagnostic testing other than CRP and related medical consumption from participating patients' electronic medical records over 28 days follow-up. A societal perspective will be used for the economic evaluation. Thus, for all four groups, in addition to costs to the health care system, we will take into account medical costs borne by patients and production costs due to illness related absence from work. Use of health care facilities will be prospectively recorded in a standardised way including all re-consultations, telephone consultations, out-of-hours consultations, and hospital admissions, (repeat) prescription of antibiotics (type, dosage, duration) and additional diagnostic tests, including bacteriological culture and X-ray. A patient diary will be the basis for assessing actual medication use, other medical costs to the patient, and absence from work[37].

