### Analysis

Statistical analyses will be performed with the aid of the SPSS and STATA statistical packages. The primary analysis will be intention to treat and will compare the marginal effects of the two interventions on antibiotic prescribing at the index consultation and incorporate an interaction effect. The interaction term will be included to test for a synergistic or antagonistic relationship between the two interventions. This will be tested using a three level logistic regression model to account for variation at the practice/GP/patient. If there is no indication of random effects at a GP level, then this will be reduced to a two level model with GP seen acting as a patient level covariate.

A four level linear regression model will be fitted to the symptom scores (logged) to account for practice, GP, patient and repeated assessments over time. The correlation between repeated assessments within individual patients will be modelled to allow for greater correlation between assessments, which are closer in time. The effect of interventions would be seen in the comparison of the slopes of symptom scores over time in the groups, i.e. having faster (or slower) recovery rates[38]. Sensitivity analyses on the symptom scores will be undertaken to assess the impact of loss to follow-up by either interpolating from available data using the estimated slope of symptoms from the model or using last value carried forward. The later is unlikely to arise in practice for an acute infection, however provides a useful extreme bound in which to interpret results.

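### Last value carried forward does not bound the between-group difference in symptom slopes, and neither planned sensitivity analysis lets missing patients in one group recover worse than in another

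*Protocol article*

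**What the plan says.** Clinical recovery is the first secondary outcome ("Clinical recovery and return to usual activities"), and the Data collection section rests it on the patient diary: "The clinical effectiveness analysis will be based on diary responses". The Analysis section fixes the model: "A four level linear regression model will be fitted to the symptom scores (logged) to account for practice, GP, patient and repeated assessments over time". It also fixes the measure of effect: "The effect of interventions would be seen in the comparison of the slopes of symptom scores over time in the groups".

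For loss to follow-up, the same section plans sensitivity analyses by "interpolating from available data using the estimated slope of symptoms from the model or using last value carried forward". It comments on the carried-forward version: "The later is unlikely to arise in practice for an acute infection, however provides a useful extreme bound in which to interpret results". Nothing in the section treats the groups differently when values are filled in.

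The Background of the abstract says that communication training "could lead to a decrease in antibiotic prescribing, without compromising clinical recovery". No margin for recovery is stated. The 90% follow-up rate under Sample size calculation refers to antibiotic prescribing; no diary completion rate is given.

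**The concern.** Carrying the last score forward assumes that a patient stops improving on the day the diary stops. For one patient with a self-limiting infection that is pessimistic, although not the worst case, since a patient may also get worse. The trial does not report one patient's course, though. It compares slopes between groups, and LVCF flattens the slope in every group. What happens to the difference depends on how much each group loses, and when.

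The other analysis offers little contrast. A mixed model fitted to the available diary days already relies on missing at random. Filling the gaps from that model's slope puts missing patients on the path the model had assumed for them.

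At stake is how the recovery result is read. If the interventions reduce antibiotic use, readers will ask whether recovery slowed. A reader told that LVCF is the extreme case would take a null result under it as the hardest test passed. The trial is open, so diary completion could plausibly differ between groups.

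**Working it through.** The article gives no symptom slope, diary-loss rate or recovery margin, so there is no figure of its own to reproduce. The inputs below are assumptions, apart from the 28 days (Data collection) and the linear model on logged scores with slope comparison (Analysis).

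**Inputs.** Days 0 to 28. Log-score slopes: control b_C = -0.12 per day, intervention b_I = -0.10 per day (slower recovery, true difference +0.020), or -0.12 in both (no difference). Loss fraction f of 10, 20 or 30%, unrelated to the patient's course. Last diary day L uniform on days 4 to 14, or on days 1 to 27 as a milder alternative. Differences are intervention minus control; positive means slower recovery with the intervention.

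**Step 1: what LVCF does to one dropout.** The filled series is b × min(t, L). Its least-squares slope is b × R(L), with R(L) = Σ(t - 14) × min(t, L) / 2030, where 2030 = Σ(t - 14)². This gives R(4) = 0.064, R(9) = 0.251 and R(14) = 0.500. The mean of R is 0.264 over days 4 to 14 and 0.500 over days 1 to 27.

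**Step 2: what it does to a group.** The expected slope is b × (1 - f × k), with k = 1 - mean R. So k = 0.736 for days 4 to 14 and 0.500 for days 1 to 27.

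**Step 3: real difference of 0.020, equal loss.** LVCF returns 0.020 × (1 - f × k).

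| Loss in each group | Days 4-14 | Days 1-27 |
|---|---|---|
| 10% | 0.0185 | 0.019 |
| 20% | 0.0171 | 0.018 |
| 30% | 0.0156 | 0.017 |

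The supposedly extreme analysis makes slower recovery look smaller.

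**Step 4: no real difference, unequal loss.** LVCF returns 0.12 × k × (f_I - f_C).
- Intervention 10%, control 20%: 0.12 × 0.736 × (-0.10) = -0.009, a false benefit of 7% of the slope. For days 1 to 27 it is -0.006, or 5%.
- Intervention 10%, control 30%: 0.12 × 0.736 × (-0.20) = -0.018, or 15%. For days 1 to 27 it is -0.012, or 10%.
- Swapping the loss rates reverses the sign and gives false harm of the same size.

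**Step 5: real difference of 0.020, unequal loss.** LVCF returns b_I(1 - f_I × k) - b_C(1 - f_C × k). For days 4 to 14:
- Intervention 10%, control 20%: -0.0926 + 0.1023 = 0.010.
- Intervention 10%, control 30%: -0.0926 + 0.0935 = 0.001.
- Intervention 30%, control 10%: -0.0779 + 0.1112 = 0.033.

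For days 1 to 27 the three results are 0.013, 0.007 and 0.029.

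**Step 6: the scenario outside both analyses.** Let both groups show a slope of -0.10 while observed and lose 20% over days 1 to 27. Missing controls keep recovering, but missing intervention patients stop improving. The true difference is 0.20 × 0.500 × 0.10 = 0.010 per day. If they worsen by 0.03 per day, it is 0.20 × 0.500 × 0.13 = 0.013. LVCF flattens both groups equally and returns 0. Filling in from the model slope puts both groups on -0.10 and also returns 0.

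**The case against.** The authors already say that LVCF is unlikely to be realistic and offer it only as an aid to interpretation. The mixed model stays the main analysis. For an individual's course, no further recovery is a fair reading of an extreme. The shifts are modest when loss is low: since k cannot exceed 1, equal loss f shrinks a difference by at most f, and a 10-point imbalance creates at most 10% of the slope. Recovery is secondary, is framed in both directions (faster or slower), and is not the only evidence on harm. Re-consultation and later antibiotics come from medical records that do not depend on diary return. The Patient follow-up section also plans a telephone call within four days and two later reminders.

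Most of this stands and limits the weight of the point. It does not rescue the stated property, because the article names the slope comparison as the effect and LVCF does not bound it.

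A reader might infer three stronger things that the article does not support.
- That the planned analyses cannot reveal slower recovery at all. They can lean that way: with more loss in the intervention group, LVCF exaggerates slower recovery (0.033 against a true 0.020 in step 5). The fault is that the direction depends on which group loses more.
- That filled-in values will be treated as observed and the standard errors will be too small. The article does not say how the uncertainty of the filled-in values is handled.
- That a formal no-harm claim fails. There is no margin and no non-inferiority test, and the phrase "without compromising clinical recovery" is a background expectation about communication training.

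**Conclusion.** The point holds as a fault in a stated interpretation. Depending on loss by group, LVCF can shrink a true slope difference, create one or exaggerate one. Filling in from the model slope adds little, because it largely repeats the main model's assumption. Neither analysis lets missing patients in one group recover worse than those in another.

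The size rests on assumed slopes, loss rates and dropout days, and on loss unrelated to outcome in steps 3 to 5. In that range, equal loss of 10 to 30% removes 5 to 22% of a real difference. A 10- or 20-point imbalance creates a false difference of 5 to 7% or 10 to 15% of the slope. Low and balanced diary loss would make the distortion small. The wording is worth correcting, but it concerns the robustness of a secondary result and leaves the primary analysis of antibiotic prescribing untouched.

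**What to change.** 1. Keep the mixed model on logged scores as the main recovery analysis.
2. Delete the statement that LVCF gives an extreme bound. LVCF may stay as a descriptive check, reported beside diary loss by group and by day.
3. Add a delta-adjusted (tipping-point) sensitivity analysis for each marginal comparison: CRP against no CRP, and communication training against none. Impute missing diary days under missing at random, with the 28-day record data (re-consultation, antibiotic prescription) as auxiliary variables. Then worsen the imputed scores in steps, only in patients allocated to the intervention under test, and report the shift at which the recovery conclusion changes. In the 2×2 layout, that intervention group includes the practices allocated to both interventions, and the plan should say so.

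The cost is a change of wording and some extra programming. The record data are already to be collected, so no new data are needed.

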## Discussion

This trial will be the first randomised controlled trial to evaluate the use of point of care CRP testing and enhanced communication skills training, on the management of acute cough due to LRTI in primary care. Both are promising interventions in reducing unnecessary antibiotic prescribing. A systematic evaluation in daily general practice is required to assess effectiveness. Our inclusion criteria are quite broad as a reflection of daily practice. LRTI is such a commonly seen illness among the full range of patients in primary care that we think the inclusion criteria should enable us to investigate all these patients. Primary inclusion criterion is the GP's suspicion of LRTI being the primary cause of the acute cough episode. GPs are daily facing difficulty in deciding upon management for these patients. The pragmatic approach of this trial leaves them very close to daily practice when considering recruiting the patient for this study. We did however define a group of focal and a group of systemic signs and symptoms in the inclusion criteria, which indicate that this patient has signs and symptoms of an infection of the lower respiratory tract.

A low CRP test result, expected to occur in at least half of these patients with LRTI, will be reassuring for both the GP and the patient that the illness is mild and most probably self-limiting. On the other end of the spectrum, very high test results will help the GP in considering antibiotic treatment or referral to a hospital. To achieve this GPs must be aware of the usefulness of the test and they should be able to properly interpret results. These are crucial conditions for a positive effect of the CRP intervention. If GPs are not aware of the value of the test, other important influences such as time pressure and patients' expectations may dilute any possible effect on antibiotic prescribing. If GPs are able to build the communication skills, which take the latter influences into account, into their routine consultations, long term competence and performance have to be monitored, since maintenance of acquired communication skills is difficult. So even when GPs understand the theory of the test and the principle of the enhanced communication, the question remains whether they will use it to adjust the management of LRTI patients.

We chose a factorial design, as it will enable us to efficiently investigate the interventions by including all participants in both analyses. Furthermore it will give us the opportunity to consider both the individual effects of both interventions and the benefits of receiving both interventions together. Factorials trials do require special considerations at the analysis stage. Interaction between the interventions needs to be investigated, since this can have effect on the power of the study[42].

In this trial both interventions are targeted at the GPs with impact on patient outcomes. Randomisation at practice level has been chosen in this trial, because there is less risk of contamination by GPs concurrently managing usual care patients, while other GPs manage their patients under the experimental regimen in the same practice. However, since patients yet have to be recruited after randomisation post-randomisation recruitment bias deserves special attention. One may expect that practices not receiving a desired intervention may gradually loose enthusiasm to recruit. As a strategem to prevent this, those practices allocated to the usual care arm, as well as those allocated to one of the arms to which only one intervention will be allocated, will be informed that they will receive a CRP device and/or the communication training after the study period. Recruitment rates across the four groups have to be monitored and baseline characteristics will be described to ensure comparability. Because of the small number of practices involved, randomisation will be restricted carefully with regard to recruitment ability. With a small number of clusters and a large number of patients this trial may be difficult to analyse and risk of loss of power exists if one practice should drop out. In cluster randomised trials the outcome for each patient cannot be assumed to be independent of that of any other patient since the patients within one cluster (practice) are more likely to have similar outcomes. Therefore multi-level analysis will be performed.

Prediction of sample size in cluster randomised trials is difficult given the fact that not only the expected effect size has to be estimated, but also the anticipated cluster size and intra-cluster correlation coefficient[43]. Despite these limitations analysis on both cluster level as well as individual level will provide us the best information on the outcome of this study[44]. Results will be reported with full transparency with regard to the factorial and cluster design[41,42].

The study will allow us to get more insight into the natural course of this common but still under-researched illness. The long follow-up of 28 days and the daily patients' evaluation of number and extent of their symptoms will provide crucial information on natural course, burden and impact on daily activities.

To our knowledge, both from the point of view of interventions and study design, this is a unique study. It will be the first to evaluate complex interventions separately and combined, that focus on the biomedical evaluation of the illness and patient centered communication. The pragmatic nature of the study, which leaves treatment decisions up to the responsible clinicians, will enhance the applicability and generalisability of findings. If these interventions decrease antibiotic prescribing and enhance patient satisfaction with favourable clinical outcomes, they could be used to enhance the quality of a large number of consultations in primary care, both for common infections and for other conditions. A full cost-effectiveness analysis to evaluate the efficiency of the interventions is needed in this regard as well and will therefore be performed. This has never been done before for an intervention to improve health care providers' communication regarding antibiotics prescribing.

If these complex interventions are shown to be effective and cost-effective, they may be refined as a result of the research and we will promote uptake in everyday care.

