## Methods/Design

This study is an open randomised controlled trial in general practice with randomisation at the practice level. The practices will be allocated to one of four groups (table 1):

**Table 1 T1:** Intervention allocation

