### Randomisation

A cluster randomised design has been chosen to avoid contamination. In order to allow assessment of the effects of each individual intervention and of combinations of interventions, compared with a control group, a factorial design for randomisation by practice will be used. Two randomisation procedures will be undertaken, one to create two groups for CRP/no CRP and a second for communication skills training/No communication skills training. The process will be stratified by the classification of the practices as above/below average for their ability to recruit patients (total number of practitioner clinics per practice per week). This will ensure a balance in recruitment potential between the two arms. Random permuted blocks of four will be generated for each randomization process. This will create two groups of 10 practices and balance at the margins for the stratification variable.

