### Patients

The GPs will approach sequential eligible adult patients during regular consultation hours. Patients are eligible if they present in general practice with an acute cough, lasting no more than 4 weeks, considered to be caused by LRTI according to the GP. In addition, the patient needs to have at least one focal and one systemic sign/symptom[33] (Figure 1). Children will not eligible, since the diagnostic value of CRP has not been investigated for LRTI in children, consultations with children and their parents will be different with respect to communication styles and strategies, and diagnostic and prognostic factors are not automatically applicable in infants. Exclusion criteria are described in figure 1.

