### CRP point of care test

20 GPs will have a CRP test device in their practice. CRP analysis will be carried out during the consultation. The NycoCard^® ^II Reader, product of Axis-Shield, will be used, in accordance with the manufacturer's instructions. The test system is based on an immunometric principle and consists of 1) a liquid for sample dilution and lysis of cells, 2) a test card with CRP-specific monoclonal antibodies coated to a membrane, 3) a conjugate solution with monoclonal antibodies coupled to ultra small gold particles and 4) a washing solution. One single drop of blood from a finger prick is needed to perform the test. A capillary collects 5 μl blood which is diluted in the 0,4 ml dilution liquid. 50 μl of this diluted sample is applied to the test well of the device. When the sample flows through the antibody-coated membrane, C-reactive proteins are forced to react and bind to the antibodies on the membrane. CRP trapped on the membrane will bind the antibody gold conjugate. Unbound conjugate is removed by one drop of washing solution. In the presence of pathological levels of CRP in the sample, the membrane appears red-brown with color intensity proportionally to the CRP concentration. The color intensity is measured quantitatively with the color densitometer NycoCard^® ^Reader II. The measuring range for whole blood samples is 8 to 250 mg/l. In the measuring range the test response is directly proportional to the concentration of CRP in the sample. For internal quality a control positive will be measured to confirm the efficacy and correct performance of the test. The control liquid is supplied with every test kit and will be run after opening of a new kit, which is once in every 24 regular tests. CRP measurements with Nycocard^® ^have proven to be valid and robust in general practice[34]. The result will be available within three minutes. This means that GPs can use the test result within the consultation. The 20 GPs who are allocated to the CRP intervention will be given guidance about the interpretation of CRP results. This information will include a comprehensive summary of the literature on LRTI and the role of CRP. We will not instruct the GPs in a prescription style fashion. Focus will be on informing them on the additional diagnostic value of CRP in ruling out pneumonia. GPs will decide on management including possible antibiotic treatment in every patient. CRP may complement their clinical findings and help in deciding upon diagnosis and treatment. The desk reminder for CRP interpretation in LRTI can be seen in figure 2. Practice assistants will be trained to use the NycoCard^® ^II Reader by the Dutch distributor who has over 10 years of training experience. GPs and assistants will be able to consult a 24-hour helpdesk for technical assistance. Questions on interpretive issues can be submitted to the research team. For specific test handling questions, we will also create a direct telephone number connecting the assistant with a clinic where assistants have extensive experience with handling point of care CRP testing. Once the CRP devices have been installed and training sessions have been performed, practices will get a 8-week run-in period before inclusion starts for familiarisation with the device and interpretation of the results.

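### The plan names recruitment bias by unblinded GPs, but its only analytic answer is to describe baseline characteristics; no baseline-adjusted analysis of the primary outcome is stated

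*Protocol article*

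**What the plan says.** The protocol article's Methods/Design section states: "This study is an open randomised controlled trial in general practice with randomisation at the practice level". Under Patients, a cough qualifies if it is "considered to be caused by LRTI according to the GP", with at least one focal and one systemic sign or symptom. Under Data collection, recruitment takes place at the visit itself: "During this consultation, the GP will take written consent and note the inclusion criteria on the trial inclusion form". Under CRP point of care test, "CRP analysis will be carried out during the consultation". The primary outcome, immediate antibiotic prescribing, arises at that same visit.

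The Discussion acknowledges the consequence: "since patients yet have to be recruited after randomisation post-randomisation recruitment bias deserves special attention". Its response has two parts. Practices that lack one or both interventions are told that they will receive them after the study. In addition, "Recruitment rates across the four groups have to be monitored and baseline characteristics will be described to ensure comparability".

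Under Analysis, the primary analysis will "compare the marginal effects of the two interventions on antibiotic prescribing at the index consultation" and include an interaction, in a three-level logistic model (practice, GP, patient). GP becomes a covariate if there is no GP-level random effect. Patient and practitioner demographics are left to exploratory analyses. Under Randomisation, "The process will be stratified by the classification of the practices as above/below average for their ability to recruit patients"; the stated primary model does not mention this factor.

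**The concern.** Cluster randomisation balances practices, not the patients whom each GP later chooses to include. Here the person choosing knows the allocation, applies a largely subjective criterion, and may already have a CRP result when completing the inclusion form, because the text does not give the order of steps. Training could also change whom a GP regards as having LRTI. The Background reports that the test was overused in mild infections in Scandinavia. That concerns testing rather than trial recruitment, but it makes a different case mix in CRP practices plausible.

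If one side recruits milder patients, it will prescribe fewer antibiotics whether or not the intervention works, and an unadjusted comparison would credit or debit that difference to the intervention. The article identifies this bias and then relies on a description of baseline data to secure comparability, which a description cannot do.

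**Working it through.** **1. The plan's own figures.** The Sample size calculation section gives 175 patients under individual randomisation, 20 practices, ICC 0.06, 350 patients after inflation, and a target of 400.

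- Cluster size: 350 / 20 = 17.5.
- Design effect: 1 + (17.5 − 1) × 0.06 = 1.99.
- Inflated size: 175 × 1.99 = 348, against the stated 350.
- Allowance for 90% follow-up: 350 / 0.9 = 389, against the stated 400.

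These figures are consistent. The point does not depend on them, but the design effect is used in step 4.

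**2. What each safeguard covers.**

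| Safeguard | Section | Acts on |
|---|---|---|
| Sequential approach | Patients | Patients already judged eligible by the GP |
| One focal and one systemic sign or symptom | Patients | A minimum, not equal severity above it |
| Delayed access to the interventions | Discussion | Willingness to keep recruiting |
| Monitoring of recruitment rates | Discussion | Number recruited |
| Stratification by number of clinics per week | Randomisation | Practice recruitment capacity |
| Description of baseline characteristics | Discussion | Detects imbalance, with no stated consequence |

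Most of these act on how many patients are recruited. None is an analytic correction for which patients are recruited.

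**3. How large a case-mix bias could be.** The documents give no severity distribution and no prescribing rate by severity, so the inputs here are assumptions. With no true effect:

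spurious risk difference = (difference between sides in the share of severe patients) × (prescribing rate in severe minus rate in mild patients)

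| Assumed gap, severe v mild | 10-point shift | 20-point shift |
|---|---|---|
| 20 points (90% v 70%) | 2 points | 4 points |
| 30 points (95% v 65%) | 3 points | 6 points |
| 40 points (90% v 50%) | 4 points | 8 points |

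Against the planned reduction from 80% to 60%, this is 2/20 = 10% to 8/20 = 40% of the target effect. The sign depends on which side recruits the milder patients. To mimic the whole 20 points, the shift would have to be 0.20 / 0.40 = 50 points at the widest assumed gap, or 0.20 / 0.30 = 67 points at the middle one.

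**4. Effect on the error rate.** Take 350 analysed patients (175 per side), 80% prescribing on both sides and a design effect of 1.99:

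SE = √(2 × 0.80 × 0.20 / 175 × 1.99) = 0.060

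By the normal approximation, the chance of rejecting at two-sided 5% with no true effect is about 8% for a 3-point bias, 17% for 6 points and 26% for 8 points.

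**The case against.** The strongest reply is that the article does not rule out adjustment. It names the effects of interest and the levels of the model, it is a condensed account, and an analysis plan that is not shown may list covariates. That stands as far as it goes: a missing covariate list would not be a finding in itself. It does not rescue the Discussion sentence, which names a bias and offers description as the means of securing comparability. Nor does it change the fact that the only covariate work mentioned is exploratory and confined to demographics.

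A reader might infer several stronger points that the documents do not support:

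- *That the estimate will be biased in favour of the interventions.* No differential selection is shown, and GPs could select in either direction.
- *That nothing else protects recruitment.* The safeguards listed above are real, though they mostly concern volume.
- *That omitting the stratum lets selection bias in.* The stratum is practice recruitment capacity. Including it would not correct the choice of patients within practices.
- *That chance imbalance with 10 practices per side is a further bias.* It is variance, which the ICC and the multilevel model already carry.

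Two further objections stand in part. Signs and symptoms are recorded after randomisation by the same unblinded GP, so adjusting for them may not be neutral and cannot remove selection on unrecorded factors. The article says only that the GP notes the inclusion criteria, so it is not certain that values such as cough duration are captured. Both are reasons to report adjusted and unadjusted results together. Finally, the flow chart is not shown and may already give the order of consent and CRP testing.

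**Conclusion.** The point holds in a limited form. The plan recognises post-randomisation recruitment bias, its only analytic response cannot do what is claimed for it, and the stated primary model has no baseline prognostic covariate. A case-mix difference could therefore pass unadjusted into the primary estimate.

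This is a risk of unknown size and direction, not a demonstrated bias. The range of 2 to 8 points rests entirely on assumed prescribing gaps of 20 to 40 points and assumed shifts of 10 to 20 points. Within that range the bias would not by itself produce the planned effect, but it could noticeably distort an estimate or a test. The change is worth making because it is cheap and protects the primary result.

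**What to change.** 1. In the Discussion, say that baseline characteristics are described to assess comparability, not to ensure it.
2. Under Analysis, pre-specify a baseline-adjusted analysis of immediate prescribing, either as the primary model or as a named sensitivity analysis reported beside the unadjusted one. Use a short fixed list of patient variables available at inclusion, such as age, cough duration, and focal and systemic signs and symptoms. Confirm that the inclusion form records these as values.
3. Under Data collection, state that eligibility, consent and the inclusion form are completed before any CRP result is known, unless the flow chart already says so.
4. Separately, include the recruitment-ability stratum in the model, for precision and correct error rates rather than for selection bias.

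The cost is a few lines of text, one degree of freedom for the stratum and a few more for the patient variables. The adjusted odds ratio is conditional, so marginal risk differences should be reported beside it. Adjustment reaches only the factors that the unblinded GP records, and the report should say so.
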